### Study Aims

This study aims to comprehensively evaluate the effects of acupoint massage, the external application of mirabilite, and their combined intervention on gastrointestinal function recovery in children following ERCP procedures. The primary objectives include comparing the efficacy of the 3 interventions—acupoint massage, mirabilite application, and the combined approach—against a routine care group, specifically in terms of shortening the time to first postoperative flatus and bowel movement. Additionally, this study aims to clarify whether the combined intervention offers advantages over individual therapies to determine the optimal clinical strategy. The secondary objectives involve assessing the degree of improvement in postoperative symptoms, including PONV; analyzing changes in inflammatory markers, including serum amylase and WBC count; and verifying the safety of the interventions regarding issues such as skin irritation and procedural tolerance. This research not only determine the optimal strategy to address the existing evidence gap in accelerated recovery following pediatric ERCP but also provides a scalable, standardized protocol for rapid postoperative recovery in pediatric patients.

## Methods

### Study Design

A parallel 4-group, single-blind, randomized controlled trial (RCT) will be conducted from November 1, 2024, to October 30, 2026. The study will take place in the pediatric department of Shuguang Hospital in Shanghai. After baseline assessments, eligible participants will be randomly assigned in a 1:1:1:1 ratio to 4 groups: acupoint massage group, mirabilite group, combination group, and conventional care group (Figure 1; Table 1). Table 2 presents the content and procedures used in each intervention group. The standardized intervention manual can be found in Multimedia Appendix 1. The primary outcome measure will be the time to postoperative gas passage or stool, whereas the secondary outcomes will include the incidence of PONV as well as changes in inflammatory markers. This study will adhere to the SPIRIT (Standard Protocol Items: Recommendations for Interventional Trials) guidelines (Multimedia Appendix 2) [22]. This protocol was registered at the International Traditional Medicine Clinical Trial Registry (ITMCTR2025000670) on April 7, 2025.

**Figure 1 figure1:**
[figure not shown]
Flow diagram of the study design. PONV: postoperative nausea and vomiting; WBC: white blood cell.

**Table 1 table1:** Clinical trial procedure.

Study period						Enrollment			Baseline (before surgery)			Intervention and assessment (after surgery)			Closeout (discharge)
**Enrollment**															
	Eligibility screen					✓									
	Informed consent					✓									
	Randomization											✓			
**Interventions**															
	Combination intervention											✓			
	Mirabilite application											✓			
	Acupoint massage											✓			
	Routine care								✓			✓			
**Assessments**															
	**General social demographic data**					✓									
		**Primary outcomes**													
			Time to first flatus							✓			✓		
			Time to first defecation							✓			✓		
		**Secondary outcomes**													
			Postoperative nausea and vomiting frequency							✓			✓		
			White blood cell count				✓			✓			✓		
			Serum amylase				✓			✓			✓		
	**Safety monitoring**														
		Skin irritation									✓			✓	
		Massage tolerance									✓			✓	

**Table 2 table2:** Intervention program.

Group	Intervention components	Frequency or duration	Key operational parameters	Safety monitoring
Acupoint massage	Stimulation of Zhongwan (CV-12), Tianshu (bilateral; ST-25), Zusanli (bilateral; ST-36), and Neiguan (bilateral; PC-6)	Twice daily (2 minutes per acupoint)	Technique: rotatory kneading+vertical pressing Pressure: ≤0.5 kg (aged 2-5 y) and ≤1 kg (aged 6-12 y) Sequence: CV-12→ST-25→ST-36→PC-6	Preprocedure wound assessment Real-time tolerance monitoring Skin response check Emergency stop for vomiting or pain
Mirabilite application	Periumbilical paste application (xiphoid process to pubic symphysis)	Twice daily (1 hour, with a 5-minute margin on either side)	Allergy test Preparation: 1:1 mirabilite: water (36 °C-38 °C) Thickness: 0.5 cm uniform layer Fixation: hypoallergenic tape Constant temperature heating pack	Preapplication skin test Temperature monitoring (36 °C-38 °C; ΔT≤1 °C) Visual inspection Discontinuation for erythema or blisters
Combination group	Both interventions	Massage: 2 per day; mirabilite: 2 per day; minimum interval: 60 minutes	Sequence: massage→mirabilite (preferred) Prohibited: massage within 1 hour after mirabilite application Separate documentation for both	Combined monitoring of both interventions

### Participants

Participants will be recruited from children who have undergone ERCP in the pediatric department of Shanghai Shuguang Hospital. Inclusion criteria are as follows: (1) aged between 2 and 12 years, (2) having completed ERCP, (3) deemed suitable for pediatric acupressure and external mirabilite application, (4) having provided written informed consent by legal guardians, and (5) having provided age-appropriate assent from the child. Exclusion criteria are as follows: (1) history of abdominal surgery or severe gastrointestinal dysmotility; (2) concomitant failure of vital organs, such as the heart, lung, or kidney; (3) known allergy to mirabilite or skin lesions contraindicating topical application; (4) cognitive or behavioral impairment that would compromise cooperation with acupressure; and (5) intraoperative conversion to open surgery due to major complications, such as perforation or severe bleeding. Participants will be withdrawn under the following circumstances: (1) voluntary withdrawal by the child or their parent; (2) loss of communication during the intervention that precludes further assessment; or (3) the occurrence of a serious adverse event, including marked clinical deterioration or an acute medical condition.

Eligible children will be identified through an electronic medical record system, with 2 senior physicians independently evaluating their enrollment criteria. In the event of disagreement, a third expert will adjudicate. All participants will have the research protocol thoroughly explained by a dedicated research nurse before surgery, and informed consent will be obtained from the guardians and the children.

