## Introduction

### Background

Endoscopic retrograde cholangiopancreatography (ERCP) is a significant minimally invasive diagnostic and therapeutic procedure extensively used in the diagnosis and treatment of pediatric hepatobiliary disorders, including common bile duct stones, biliary strictures, biliary fistulas, and chronic pancreatitis [1-3]. Research indicates that children undergoing ERCP experience varying degrees of postoperative gastrointestinal dysfunction, including delayed passage of flatus and stool, abdominal distension, nausea, vomiting, and diminished bowel sounds [2,4]. If not promptly addressed, these complications may lead to severe outcomes, such as intestinal perforation and pancreatitis [5]. Postoperative gastrointestinal dysfunction not only increases the child’s discomfort but may also prolong hospital stays, raise intravenous nutrition requirements, and heighten the risk of complications, ultimately impacting the overall recovery process and exacerbating the economic burden on health care systems [6,7].

The mechanisms contributing to gastrointestinal dysfunction following ERCP are multifactorial, encompassing preoperative anxiety, opioid use, mechanical stimulation of the intestines from surgical procedures, vagal nerve dysfunction, and postoperative inflammatory responses [8-10]. Furthermore, the gastrointestinal development of children is incomplete, and their metabolic and neuroregulatory functions are more sensitive than those of adults, potentially exacerbating the delay in postoperative gastrointestinal recovery [11,12]. Current postoperative management strategies have shown limited effectiveness in the pediatric population. For instance, the administration of low-dose opioids after gastrointestinal surgery fails to alleviate postoperative pain and is associated with an increased incidence of postoperative gastrointestinal dysfunction [9]. Currently, there is no efficient, safe, and adherence-friendly specific protocol specifically designed to enhance gastrointestinal function in children after ERCP, highlighting the pressing need to explore nonpharmacological, low-risk alternative therapies.

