Emergency response plans have been pre-established to address potential safety issues. To manage possible skin allergic reactions resulting from the external application of mirabilite, emergency medications will be readily available on-site for localized treatment; should a clear allergic reaction or severe skin irritation arise, the application of mirabilite will be immediately terminated, symptomatic treatment will be administered, and adverse events will be reported as required. If a child shows discomfort, distress, or verbal or behavioral refusal during an intervention, the procedure will be paused immediately. The researcher will comfort the child and consult with the guardian. The intervention may resume only if the distress is transient and the child and guardian agree. Continued refusal or significant distress will lead to termination of that session or withdrawal from the study. All research personnel must be thoroughly familiar with and strictly adhere to these safety protocols and emergency plans, prioritizing the safety of the children involved and promptly reporting any incidents that exceed the prescribed protocols or severe adverse events to the principal investigator and the ethics committee.

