### Data Analysis

Statistical analyses will be performed using SPSS (version 25.0; IBM Corp) and RStudio (Posit PBC), incorporating the *survival* package. A 2-sided significance level of .05 will be applied for all tests, and an intention-to-treat analysis will be implemented to handle missing data.

Categorical baseline variables will be summarized as frequencies and percentages, with group comparisons conducted using chi-square tests or Fisher exact tests as appropriate. Continuous variables will be described as mean with SD if normally distributed and compared via 1-way ANOVA; nonnormally distributed variables will be presented as median with IQR and compared using the Kruskal-Wallis *H* test. Time-to-event analysis will be applied to the primary outcomes, namely time to first flatus and time to first defecation. Cumulative event rates will be visualized using Kaplan-Meier curves, and overall, between-group differences will be assessed via the log-rank test. To address multiple comparisons, a prespecified hierarchical contrast approach will be used. Primary contrasts, including each intervention group compared to the routine care group, will be evaluated using a Bonferroni-adjusted significance threshold of .0167. Exploratory pairwise contrasts between the combination group and each monotherapy group will be conducted only if significant differences are observed in the primary contrasts. Additionally, a Cox proportional hazards regression model will be used to estimate adjusted hazard ratios with 95% CIs for each intervention relative to routine care while controlling for baseline covariates identified in univariable analysis with a *P* value of <.10.

The secondary outcome analysis will include comparisons of PONV incidence using chi-square tests, with Bonferroni-adjusted pairwise testing where applicable. Inflammatory markers, including WBC count and serum amylase, will be analyzed using repeated-measures ANOVA to evaluate changes at 3 hours after surgery and on the morning of postoperative day 1. Safety outcomes will be summarized descriptively, and between-group differences in adverse events will be examined using chi-square or Fisher exact tests.

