### Ethical Considerations

This study adheres to the Declaration of Helsinki and Chinese pediatric research ethics guidelines [27]. A structured, age-appropriate informed consent process will be implemented. Trained research nurses will explain the study purpose, procedures, risks, benefits, privacy measures, and the right to withdraw to the legal guardian. Written consent will be obtained after ensuring full understanding.

We place the highest priority on respecting the child’s own will. In accordance with established pediatric ethical guidelines, a tiered assent process will be applied [27]. Children aged between 8 and 12 years will receive a simplified explanation using age-appropriate language and visual aids, and those who demonstrate understanding will be invited to sign a child assent form. For children aged between 6 and 8 years, verbal assent will be sought using simple language, and their agreement will be formally documented. For children aged between 2 and 6 years, participation will be based primarily on guardian consent; however, researchers will continuously monitor the child’s emotional and behavioral responses. Persistent distress or clear refusal will be respected as an expression of dissent, leading to immediate pausing or adjustment of the procedures. The child’s right to refuse is absolute. Regardless of guardian consent, if a child explicitly refuses or withdraws assent at any point, their decision will be honored without exception, resulting in nonparticipation or withdrawal from the study.

Aas a token of appreciation for participation and to support ongoing engagement, each child will receive a small, age-appropriate gift upon enrollment and upon completion of the final follow-up assessment. This compensation is not contingent on study outcomes and is provided to acknowledge the time and contribution of the participants and their families.

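### The plan withdraws the child, not only the intervention, after a serious adverse event and possibly after refusal; the resulting censoring may be informative, and intention-to-treat cannot supply the missing outcomes

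*Protocol article*

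**What the plan says.** All references are to the protocol article.

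- **Participants.** "Participants will be withdrawn under the following circumstances": the family's or child's own choice; lost contact, limited to cases where the child can no longer be assessed; and "the occurrence of a serious adverse event, including marked clinical deterioration or an acute medical condition". The third reason carries no such limit.
- **Quality Control and Precautions.** "Continued refusal or significant distress will lead to termination of that session or withdrawal from the study". The same section requires every adverse event, related or not, to be documented through to its duration and outcome.
- **Ethical Considerations.** If a child explicitly refuses or takes back assent, "their decision will be honored without exception, resulting in nonparticipation or withdrawal from the study". For the youngest children, persistent distress or refusal leads to pausing or adjusting the procedure.
- **Data Analysis.** "Time-to-event analysis will be applied to the primary outcomes, namely time to first flatus and time to first defecation", by Kaplan-Meier, log-rank and Cox methods. Each active arm against routine care "will be evaluated using a Bonferroni-adjusted significance threshold of .0167". On missing data the section says only that "an intention-to-treat analysis will be implemented to handle missing data".
- **Randomization and Blinding; Primary Outcomes.** Flatus and stool are assessed every 4 hours on the ward.
- **Sample Size.** 56 children are required, raised to 72 for 20% dropout.

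**The concern.** Log-rank and Cox methods assume that a child censored at a given hour has the same outlook as those still under observation. Withdrawal triggered by clinical deterioration puts that in doubt. The Background section itself ties unresolved gut dysfunction to serious events: "If not promptly addressed, these complications may lead to severe outcomes, such as intestinal perforation and pancreatitis". A child withdrawn for such an event is plausibly a slow recoverer, and censoring removes the late time from the data.

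Loss may also differ by arm. Routine-care children receive neither massage nor mirabilite, so refusal of those procedures can arise only in the three active arms.

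The stated remedy does not help. Intention-to-treat fixes the population and the arm; it cannot replace a time of flatus or stool that nobody recorded. Nor could a statistical analysis plan, which is not shown here, recover it later. Both primary outcomes are affected.

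**Working it through.** **1. The plan's own figure.** Inputs from Sample Size: F test, 4 groups, f = 0.593, α = .05, power .95, dropout 20%. Power is the upper tail of a noncentral F with 3 and N − 4 degrees of freedom and λ = f²N.
- N = 52 (13 per group): power .946, too low.
- N = 56 (14 per group): λ = 0.593² × 56 = 19.7, power .962. The stated 56 is reproduced.
- Dropout: 14/(1 − 0.2) = 17.5, rounded up to 18; 4 × 18 = 72. The stated 72 is reproduced.

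Anticipated loss is 18 × 0.2 = 3.6 children per arm, from all causes. The inflation protects the number analysed. It does nothing about which children are lost.

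**2. The sections side by side.**
- *Serious adverse event:* Participants withdraws the child. Quality Control and Precautions still wants the event followed to its outcome. Neither says whether flatus and stool are still recorded.
- *Refusal:* Quality Control and Precautions offers ending the session or leaving the study. Ethical Considerations gives nonparticipation or withdrawal for explicit refusal, and pausing or adjustment for the youngest.
- *Feasibility:* a child still on the ward after a serious adverse event could usually still be assessed every 4 hours.

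**3. How large the effect could be.** The documents give no withdrawal rates by arm and no event times for this population, so this is illustration only. Hazard ratios are active against control with a true value of 1; above 1 means the active arm looks faster.

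*Model A.* 18 v 18 children; SD 13.03 h from Sample Size; mean 40 h assumed; withdrawn children censored uniformly at 6 to 24 h. Rejection is one-sided in favour of the active arm at .0167/2 ≈ .0083. With full data it is about .01.

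| Withdrawals | Apparent HR | Rejection |
|---|---|---|
| 1, 2 or 3, active arm only, from its slowest 2, 4 or 6 children | 1.16, 1.24, 1.31 | .029, .040, .044 |
| 1, 2 or 3, active arm only, from its slower half | 1.04, 1.10, 1.17 | .013, .020, .026 |
| 1, 2 or 3, active arm only, unrelated to recovery | 1.01, 1.01, 1.02 | .012 to .014 |
| 1 v 1 or 2 v 2, from the slowest in each arm | about 1.00 | – |
| 1 active v 2 control, from the slowest | 0.92 | – |

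A repeat of the first row gave 1.15, 1.26, 1.30 and .030, .046, .050. With 4000 runs the simulation error on a rate near .03 is about √(.03 × .97/4000) = .0027.

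*Model B.* Weibull times, shape 2, median 30 h (assumed); the slowest third at risk of withdrawal at 4 to 24 h; rejection two-sided at .0167 with 18 per arm.

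| Withdrawn, active v control | Apparent HR | Rejection |
|---|---|---|
| 0 v 0 | 1.01 | .020 |
| 5% v 0 | 1.04 | .027 |
| 10% v 0 | 1.12 | .030 |
| 20% v 0 | 1.31 | .060 |
| 20% v 10% | 1.15 | .036 |
| 20% v 20% | 1.00 | .018 |

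Both models show the same pattern. Bias needs withdrawal that is related to recovery and also unequal between arms.

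**The case against.** Several stronger readings are tempting, and the text does not carry them.

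- *That every child who keeps refusing is withdrawn.* Quality Control and Precautions lets staff end only the session, and pausing or adjusting is foreseen for the youngest.
- *That safety follow-up stops at withdrawal.* The same section requires adverse events to be recorded through to their outcome and severe ones to be reported promptly. No section says recording ends. What remains is an unresolved tension with the withdrawal rule.
- *That intention-to-treat is broken.* No section removes withdrawn children from the analysis, and they can be kept in their arm and censored. What is weakened is the assumption about censoring.
- *That the active arms will look faster.* The serious-adverse-event rule applies to all four arms. If the interventions work as hypothesised, deterioration may be commoner under routine care and the bias may run the other way. Refusal is confined to active arms, but nothing links refusing massage or paste to slow gut recovery. The figures near 1.3 require both conditions at once, and the 20% dropout allowance covers all causes in all arms.

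It is also fair that an article may leave censoring rules and sensitivity analyses to a fuller plan.

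These objections limit the size and certainty of the concern. They do not remove it. The article itself fixes a rule that withdraws the participant, leaves open whether outcome recording continues, and names a remedy that cannot work.

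**Conclusion.** The concern holds in limited form. Withdrawal after a serious adverse event plausibly makes censoring of the primary outcomes informative, and the missing-data sentence offers no protection. The case is strongest for serious adverse events. For refusal the documents support only that loss may differ by arm.

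With no true effect, the apparent hazard ratio lies between about 1.0 and about 1.3 in the scenarios where the active arm loses at least as many children as control, and reached 0.92 when more slow children left control. These values rest on assumed event times and withdrawal patterns. A reader might infer that a false-positive result is likely; the documents do not support that, because they fix neither the imbalance between arms nor the link to recovery. The sample size is not in error on this point. Should-fix, moderate confidence.

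**What to change.** 1. In Participants, separate ending the study intervention from ending follow-up. After a serious adverse event or refusal of the intervention, keep recording flatus, stool, nausea and vomiting, and adverse events to discharge, unless the guardian or child withdraws from data collection. The child's absolute right to refuse stays as it is.
2. Reconcile Participants, Quality Control and Precautions, and Ethical Considerations on what withdrawal means for outcome and safety recording. When the intervention itself is stopped is not questioned here.
3. Replace the missing-data sentence with: all randomised children are analysed in their assigned arm; a child whose follow-up truly ends is censored at the last assessment; a sensitivity analysis treats withdrawn children in every arm as event-free to the longest observed time.

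The cost is a short amendment and case report form wording. The 4-hourly assessments already exist, so no extra staff are needed and the sample size is unchanged. With 38 of 72 children enrolled as of January 2026, the change can still cover the remaining 34. Outcomes not recorded for children already withdrawn may be unrecoverable.

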### Sample Size

G*Power (version 3.1; Heinrich Heine University Düsseldorf) software was used to calculate the sample size. We used the *F* test as the method for statistical analysis, establishing an α of .05 and a power (1–β) of .95. The estimation was based on data from a previous high-quality clinical trial, which used a 3-arm parallel design evaluating combined mirabilite application with massage, massage alone, and mirabilite application alone in patients undergoing laparoscopic hepatectomy [23]. Using the reported group means, a pooled SD of 13.03 hours, and a sample size of 30 per group from that trial, the software estimated an effect size (*f*) of 0.593. On the basis of this effect size, the calculated total sample size required for this 4-group study was 56 participants. To account for an anticipated dropout rate of 20%, the final planned total sample size is 72 participants, with approximately 18 (25%) individuals allocated to each group.

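### The stated power of .95 belongs to a four-group omnibus F test, not to the primary log-rank contrasts against routine care at .0167, and its effect size comes from a trial described without a routine-care arm

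*Protocol article*

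**What the plan says.** Sample Size (protocol article, Methods) rests on an *F* test, "establishing an α of .05 and a power (1–β) of .95". The effect size comes from a trial "which used a 3-arm parallel design evaluating combined mirabilite application with massage, massage alone, and mirabilite application alone". That trial was done "in patients undergoing laparoscopic hepatectomy". The protocol takes its group means together with "a pooled SD of 13.03 hours, and a sample size of 30 per group from that trial". It then reports that "the software estimated an effect size (*f*) of 0.593". On this basis "the calculated total sample size required for this 4-group study was 56 participants", and a 20% dropout allowance takes the total to 72, about 18 per arm.

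Data Analysis (same article) treats time to first flatus and time to first defecation as time-to-event outcomes, with Kaplan-Meier curves and an overall log-rank test. It then states: "Primary contrasts, including each intervention group compared to the routine care group, will be evaluated using a Bonferroni-adjusted significance threshold of .0167". Combination versus each monotherapy is exploratory and conditional on those contrasts. A Cox model gives adjusted hazard ratios with 95% CIs for each intervention against routine care.

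The article gives no routine-care mean, no expected difference in hours from routine care, no hazard ratio, and no power for any contrast.

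**The concern.** The sizing calculation and the primary contrasts differ in three ways: the test (ANOVA F against log-rank), the hypothesis (any difference among four means against one named arm versus routine care) and the alpha (.05 against .0167). The effect size adds a fourth gap. An f computed from three active arms measures how far those arms differ from one another. It says nothing direct about how far any of them lies from routine care, which is what every primary contrast tests.

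At stake is how the monotherapy results will be read. Study Aims sets out to compare each intervention with routine care, and the Discussion says the design separates the contribution of each component. If a massage or mirabilite contrast is not significant, a reader who sees .95 in the sample size section may take that as good evidence of no effect, although the contrast may have had much less power.

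**Working it through.** **1. The plan's own figure.** Inputs from Sample Size: k = 4, f = 0.593, alpha = .05, target power .95. Noncentral F with ncp = f² × N and df = 3 and N − 4:
- N = 52: power .946
- N = 56: power .962

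So 56 is the smallest equal-group total that reaches .95, and the stated figure reproduces. Dropout: 56/0.8 = 70, and the next multiple of 4 is 72. At N = 72 the omnibus F test has power .991. With 20% loss, 72 × 0.8 = 57.6, or about 14 per arm. I therefore use 14 and 18 per arm below.

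**2. Converting f to hours.** f = (SD of group means)/(within-group SD), so the SD of means is 0.593 × 13.03 = 7.73 h. To get differences from routine care, a pattern of means must be assumed. Introduction (Background) hypothesises that all three interventions beat routine care and that the combination is best, but gives no sizes.

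Reading A, f = 0.593 taken as the spread of all four arms of this trial:
- Monotherapies midway, means proportional to (2, 1, 1, 0), SD 0.7071: step 7.73/0.7071 = 10.9 h (d = 0.839). Combination differs from routine care by 21.9 h.
- Four equally spaced means (3, 2, 1, 0), SD 1.118: step 7.73/1.118 = 6.9 h (d = 0.530). Differences are 6.9, 13.8 and 20.7 h.
- All active arms equal (1, 0, 0, 0), SD 0.4330: difference 7.73/0.4330 = 17.8 h (d = 1.369) for every contrast.

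Reading B, f = 0.593 taken as the spread of the three active arms, as the section describes it. With equal monotherapies (1, 1, 0), SD 0.4714, the combination is 7.73/0.4714 = 16.4 h ahead of each monotherapy. Assume also that each monotherapy is 16.4 h ahead of routine care (d = 1.258). The four-arm f is then 0.7071 × 16.4/13.03 = 0.89.

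**3. Power per contrast at two-sided .05/3 = .0167.** The t-test power uses noncentral t with ncp = d√(n/2) and df = 2n − 2. Log-rank power is by simulation with normal times, SD 13.03 h and no censoring. Rounding times up to a 4-hour grid changes little.

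| Assumption | Contrast with routine care | t test, 14 / 18 per arm | Log-rank, 14 / 18 per arm |
|---|---|---|---|
| A, midway | each monotherapy | 38% / 51% | about 37% / 45% |
| A, midway | combination | 96% / 99% | about 94% / 98% |
| A, equally spaced | weaker monotherapy | 14% / 19% | about 15% / 19% |
| A, equally spaced | stronger monotherapy | 60% / 74% | about 56% / 70% |
| A, equally spaced | combination | 94% / 99% | about 91% / 97% |
| A, all active equal | every contrast | 85% / 94% | about 80% / 90% |
| B, 16.4 h step | each monotherapy | 77% / 89% | about 73% / 86% |

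**4. Detectable difference, one contrast, t test at .0167.**
- 80% power: 16.9 h (14 per arm) or 14.7 h (18 per arm)
- 95% power: 21.1 h (14 per arm) or 18.3 h (18 per arm)

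**5. The same on the hazard-ratio scale.** Schoenfeld: power = Φ(ln HR × √(D/4) − 2.394), with D = 28 or 36 events if every child has the event.
- HR 2.0: 29% / 38%
- HR 3.0: 70% / 82%
- HR needed for 80%: about 3.4 / 2.9
- HR needed for 95%: about 4.6 / 3.8

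The .0167 threshold is used as stated, with no further allowance for there being two primary outcomes.

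**The case against.** The strongest reply is that any single low figure is as poorly supported as the .95. A reader might infer that a monotherapy contrast has only about 35-50% power. The documents do not establish that. The figure needs f = 0.593 to be the four-arm spread and the monotherapies to lie midway, and neither is stated. If f does not inform the routine-care difference, it cannot be used to fix that difference at 10.9 h either. Reading B uses f as documented and gives about 73-86%. This stands, and it is why only a range is given.

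A reader might also infer that .95 is out of reach for all three contrasts whatever the truth. That holds for the patterns above with the four-arm f at 0.593, but nothing makes 0.593 a ceiling. If routine care is slower than every active arm, adding it can raise the four-arm f, as in Reading B (0.89). Gaps of 18.3 to 21.1 h would give 95% per contrast.

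The omnibus calculation is not unrelated to the plan: an overall log-rank test is planned, and it is the time-to-event counterpart of the F test. Nor does the article say that non-significance will be read as no effect. Hazard ratios with CIs against routine care are already planned, and the three source arms are listed openly. These points lower the severity, but they do not make .95 the power of the primary contrasts.

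This is not a detail left to an analysis plan. The article prints both the calculation and the contrasts, and they do not match.

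**Conclusion.** The mismatch is certain from the text. The .95 applies to a four-group F test at .05 with f = 0.593, and not to log-rank contrasts with routine care at .0167. The N of 56 is correct for the test it names.

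The size of the shortfall is uncertain, because no routine-care difference or hazard ratio is given. Across the assumptions tried, log-rank power for a monotherapy contrast runs from about 15% to about 90%. With the four-arm f held at 0.593, none of the patterns gives .95 for all three contrasts; a larger routine-care gap could. The doubt falls mainly on the monotherapies: combination versus routine care keeps about 91-98% by log-rank under the two graded Reading A patterns, and about 80-90% if all active arms are equal.

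This should be fixed. It concerns what the power statement means and how null results will be read. It does not show that the trial's size is wrong.

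**What to change.** Keep N = 72 and revise the text:

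1. In Sample Size, state that power .95 refers only to the omnibus four-group F test at alpha .05 and f = 0.593.
2. State that the source trial, as described, had no routine-care arm, so its f does not estimate any difference from routine care.
3. Report the power of each primary log-rank contrast at .0167 for 14 and 18 children per arm, as a range under named assumptions about the routine-care difference. Give the difference in hours detectable at 80% (about 14.7 to 16.9 h by t test).
4. In Data Analysis, commit to interpreting a non-significant monotherapy contrast through the planned hazard ratio and its CI, and not as evidence of no effect.

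The cost is rewording and a less favourable power statement. No patients, tests or thresholds change. The article reports 38 children randomized and no interim analysis as of January 2026, so on that account the correction can be made before results are known.
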